### Sample size

We determined power calculations prior to the main study to determine the optimal sample size using a mixed-procedure in SAS (multi-level model, restricted ML-estimator). The required number of participants was calculated based on the estimated effect upon control competence for physical training and health-related fitness knowledge by considering available data from previous studies. We determined that a difference of d = 0.30 between the intervention (IG-run, IG-game play) and control groups (CG-run, CG-game play) should be identified with ≥80% power and a 0.05 one-sided significance level. If we assume that an average PE class contains 26 students, the study would require at least 10 PE classes in each group (IG-run, IG-game play, CG-run, CG-game play) according to the power analysis. Therefore, we added four additional classes per intervention group to avoid a reduction in statistical power if a class would withdraw from the study.

### Randomization

We randomly assigned participants to either the control (CG-run, CG-game play) or the experimental conditions (IG-run, IG-game play). Due to gender-segregated PE classes in Baden-Wuerttemberg, we conducted separate randomization procedures within the gender strata. This investigation had three study periods (Waves 1–3); therefore, we designed the randomization procedure to be performed in three blocks of 16 PE classes. The allocation ratios differed between these three study periods. In Waves 1 and 3, we randomly and equally allocated both male and female PE classes to the four study groups (1:1:1:1). For Wave 2, we used unequal allocation at a ratio of three (IG-run): three (IG-game play): one (CG-run): one (CG-game play). The randomization took place prior to each study period according to the guidelines of Hutchinson and Styles in 2010 [32]. An independent staff member who was not involved in this study used a computer to generate random numbers for each PE class separated by gender and then sorted the cases according to their random numbers. As a result, the allocation to the different study groups remained concealed to the researchers. Table 1 summarizes the allocation ratios as well as the planned number of female and male PE classes separated by study wave.

**Table 1 Tab1:** The planned and effective allocation of the study groups separated by gender and wave

	Allocation ratio and planned number of PE classes		Effective allocated number of participating PE classes after randomization (number of participating students)									
			Male					Female				
Wave	IG-run : IG-game play : CG-run : CG-game play	male/female classes	IG-run (n)	IG-game play (n)	CG-run (n)	CG-game play (n)	Total	IG-run (n)	IG-game play (n)	CG-run (n)	CG-game play (n)	Total
Wave 1	1:1:1:1	8/8	2 (24)	2 (30)	2 (24)	2 (33)	8	2 (45)	2 (34)	2 (25)	2 (31)	8
Wave 2	3:3:1:1	8/8	2 (33)	2 (41)	0 (0)	1 (23)	5^a^	3^b,c^ (56)	2^b^ (39)	0^b^ (0)	1 (24)	6
Wave 3	1:1:1:1	8/8	3 (55)	2 (35)	3 (50)	3 (63)	11^d^	2 (42)	3 (57)	3 (51)	2 (45)	10^d^
Sum		48	7 (112)	6 (106)	5 (74)	6 (119)	24	7 (143)	7 (130)	5 (76)	5 (100)	24

^a^As the recruitment rate had been lower than expected, randomization was conducted with five classes and three additional dummy classes to compensate for the absent three male PE classes

^b^After randomization three female classes allocated to IG-run, IG-game play and CG-run canceled their participation. Therefore, they are not considered in the labeled columns

^c^One female PE teacher could be recruited after randomization. She was allocated to the group of PE teacher who canceled her participation at first (IG-run)

^d^In addition to the listed number of PE classes one male and two female dummy classes were added to randomization to guarantee equal allocation ratio

In Wave 2, we were unable to recruit the intended number of PE classes (8 female and 8 male PE classes). Prior to the study period 2, only 8 female and 5 male PE classes indicated their willingness to take part in this study. Therefore, only 13 PE classes were considered in the randomization. In addition, after we had completed the randomization process, three female PE teachers withdrew their participation. To compensate, another female PE teacher who agreed to take part in the study was allocated to the respective study group. Consequently, only 11 of the 16 expected PE classes (5 male and 6 female PE classes) participated in Wave 2. Once Wave 3 began, we recruited 21 PE classes (10 male and 11 female PE classes) to compensate for the absent PE classes in Wave 2 and also to reach the goal of 48 PE classes. To maintain an equal allocation ratio, we added three dummy PE classes (2 male and 1 female classes) for the randomization process. As a consequence, the effective number of PE classes varied between 2 and 3 classes per group. Table 1 shows the final result of the randomization process.

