**Design/methods:**

This study is a cluster randomized controlled trial that compares two physical education intervention programs on health and physical fitness (IG-run, IG-game play) with regular physical education lessons (CG-run, CG-game play) in secondary schools in Germany. Forty-eight physical education classes (ninth grade) were recruited and randomly allocated to the four study groups. The intervention programs include six physical education lessons on health and physical fitness and only differ in the type of physical activity that is executed (running and jumping vs. small-sided games). The students’ PAHCO is examined both pre- and post-intervention and after 8–12 weeks of follow-up. We also determine various process variables during the intervention period to analyze the intervention fidelity.

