## Methods

### Design

The GEKOS study is a cluster randomized controlled trial that includes two intervention groups (IG-run, IG-game play) and two wait-list control groups (CG-run, CG-game play). The study is designed to investigate the superiority of an intervention compared to a control condition. Overall, we recruited 48 ninth grade PE classes and their PE teachers for this study. At this age, boys and girls in the federal state of Baden-Wuerttemberg (Germany) take separate PE classes, so we studied 24 male classes and 24 female classes. We randomly allocated the participating classes to the different study conditions stratified by gender. In order to gain more information about the quality of the intervention delivery, the relative number of classes differed between IG and CG. Accordingly, 14 classes were planned to be allocated to each intervention group prior to the intervention study, whereas 10 classes were to be placed into each control group. Further, teachers were not blinded to the study conditions as they received instructions about the intervention and control conditions prior to the study. Figure 1 illustrates the number of classes (c) and students (*n*) planned to be allocated to the different study conditions.

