### Recruitment

The heads of the regional school boards of Baden- Wuerttemberg were the main gatekeepers for recruitment. In preparation for each study wave, we asked the heads of the school boards three to four months in advance to contact the school principal and the teachers who are responsible for PE at their schools (PE subject coordinators) and to invite them to participate in the study. Additionally, the main researchers contacted PE teachers at schools that participated in pilot studies and also former PE students at a University in Germany. During recruitment, interested PE teachers received detailed descriptions of the study and an information sheet to share with their school principals. We informed those who agreed to participate in the study about group allocation as soon as we completed our randomization procedures. These teachers also received informed consent forms for their students and a timetable with the proposed measurement points for the pre-, post-, and follow-up assessments. We used the same recruitment process for all three study waves.

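### The abstract and Design section call all 48 participating classes randomly allocated, but one IG-run class was added after randomisation with no reported random draw, so 47 of 48 were randomised

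*Protocol article*

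**What the plan says.** The abstract states that "Forty-eight physical education classes (ninth grade) were recruited and randomly allocated to the four study groups". The Design section says the same in general terms: "We randomly allocated the participating classes to the different study conditions stratified by gender". The Randomization section closes by presenting Table 1 as the end product of randomisation, with 48 classes in total and 14 in IG-run.

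The notes to Table 1 give a different account of Wave 2. Footnote b: "After randomization three female classes allocated to IG-run, IG-game play and CG-run canceled their participation". Of these classes it adds: "Therefore, they are not considered in the labeled columns". Footnote c: "One female PE teacher could be recruited after randomization", and then "She was allocated to the group of PE teacher who canceled her participation at first (IG-run"). The running text of the Randomization section confirms the three withdrawals and the one replacement.

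On timing, the Recruitment section says: "We informed those who agreed to participate in the study about group allocation as soon as we completed our randomization procedures".

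The Data analysis section compares each intervention group with its own control group. It describes intention-to-treat as analysing classes and students by study group, and commits to the CONSORT statement for cluster trials.

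**The concern.** The summary statements claim a design property, random allocation of every participating class, that the article's own footnotes contradict for one class. The procedure in the Randomization section (an independent staff member, computer-generated numbers, allocation concealed from the researchers) cannot describe a class recruited after the draw and put into a known vacancy.

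The class sits in one arm of a main comparison, IG-run versus CG-run. Places were vacant in IG-run, IG-game play and CG-run, and no draw among them is reported. Table 1 shows no CG-run class in Wave 2 for either gender, so the late class has no same-wave control. If a teacher joins when her place is already fixed, willingness to deliver that programme can influence who joins. The article itself treats teachers' attitudes as a possible influence on the quality of delivery. Taken at face value, an analysis by study group would include this class as if it had been randomised.

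**Working it through.** **Inputs.** Class and student counts come from Table 1. The Wave 2 and Wave 3 recruitment figures and the 3:3:1:1 ratio come from the Randomization section. The difference d = 0.30 and the one-sided 0.05 level come from the Sample size section. The intraclass correlation (ICC) is not given, so a range is assumed. The late class's size is not given either; it is taken as the mean of its Table 1 cell, 56/3 = 18.7 students.

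**1. The stated total.** Summing Table 1 over gender and wave gives IG-run 14 (255 students), IG-game play 13 (236), CG-run 10 (150) and CG-game play 11 (219). That is 48 classes and 860 students, so the article's 48 is reproduced as the number participating.

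**2. Classes that entered the draw (dummy classes left out).**
- Wave 1: 8 + 8 = 16
- Wave 2: 8 female + 5 male = 13
- Wave 3: 21
- Total: 16 + 13 + 21 = 50

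50 − 3 withdrawn = 47; 47 + 1 added = 48. The text and Table 1 disagree on the gender split in Wave 3 (10 male and 11 female against 11 and 10), but both give 21.

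**3. Check within the Wave 2 female stratum** (order: IG-run / IG-game play / CG-run / CG-game play).
- Eight classes at 3:3:1:1: 3/3/1/1
- Less one each from IG-run, IG-game play and CG-run: 2/2/0/1
- Plus the late class in IG-run: 3/2/0/1, or 6 classes, exactly as in Table 1

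IG-run therefore holds 14 − 1 = 13 randomised classes.

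**4. Possible shift in the IG-run mean.** If the late class differs by δ from the mean of the other 13 classes, the mean of the 14 moves by δ/14.

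| δ (assumed, SD) | Shift (SD) | Share of d = 0.30 |
|---|---|---|
| 0.2 | 0.014 | 5% |
| 0.5 | 0.036 | 12% |
| 1.0 | 0.071 | 24% |

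Weighting by students (18.7/255 = 7.3%) gives nearly the same: 0.015, 0.037 and 0.073.

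**5. Power cost of leaving the class out.** SE = √{[1 + (m₁ − 1)·ICC]/N₁ + [1 + (m₂ − 1)·ICC]/N₂}, where m is mean class size and N the number of students; power = Φ(0.30/SE − 1.645). CG-run is 10 classes and 150 students. IG-run is 14 classes and 255 students with the late class, and 13 classes and 255 − 18.7 = 236.3 students without it.

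| ICC (assumed) | With | Without |
|---|---|---|
| 0.02 | 0.818 | 0.808 |
| 0.05 | 0.710 | 0.699 |
| 0.10 | 0.576 | 0.565 |

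The loss is about one percentage point throughout.

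**The case against.** The replacement is disclosed. Footnotes b and c are attached to the cells concerned and name the arms, and Table 1 is labelled as showing planned and effective allocation. This stands: nothing is hidden. A reader might infer that a CONSORT flow cannot be built from these figures, but step 2 builds it. The disclosure does not, however, correct the abstract or the Design section, which state the opposite without a qualifier.

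Detailed rules for a replacement class commonly sit in an analysis plan, which is not shown. This also stands, and the absence of such a rule is not the point. The point is the affirmative statement that all classes were randomly allocated.

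Two stronger readings are tempting. One is that the three teachers withdrew because they knew their arm. The Recruitment section says teachers were told their group once randomisation was complete, and the withdrawals came after randomisation. But no passage says these three had been told before cancelling, or why they cancelled, and they came from three different arms. The other is that the late teacher joined knowing she would deliver the intervention, or that the team chose her arm. The text mentions her agreement and then her allocation, and footnote c can be read as a fixed rule of filling a vacated place. That is not random, but it is not shown to be discretionary.

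The larger shifts are also unlikely if classes vary little. Ten against ten classes of 26 reach 80% power only if the ICC is about 0.035, since 138 students per arm suffice without clustering and (260/138 − 1)/25 = 0.035. The between-class SD is then √0.035 ≈ 0.19, which puts a true class deviation of 0.5 SD about 2.7 such SDs out, before any baseline adjustment. This argues for the lower part of the range.

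**Conclusion.** The statement that all 48 participating classes were randomly allocated is wrong by the article's own account. Fifty classes were randomised, 3 withdrew afterwards, 47 participated as randomised, and 1 was added to IG-run with no reported random draw. These counts rest on the documents alone.

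The consequence for the estimate is a modest risk of bias confined to IG-run versus CG-run. The late class is 1 of 14 IG-run classes (7%). The shift of 0.014 to 0.07 SD depends on an assumed deviation of 0.2 to 1.0 SD, for which the documents give no basis. Selection by willingness is possible but not established. The 47 classes are not a strict intention-to-treat set either, because three randomised classes are missing from them.

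**What to change.** Correct the abstract, the Design section and the text around Table 1 to say: 50 classes randomised, 3 withdrew after randomisation, 47 participated as randomised, 1 added without randomisation. Keep footnotes b and c, and show the three withdrawn classes by arm in the flow diagram.

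Report IG-run versus CG-run on the randomised participating classes (13 against 10) alongside the result that includes the late class (14 against 10). Describe the former as randomised participating classes, not as intention-to-treat.

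The cost is a few sentences and one further model run. The analysis without the class loses about 19 students (assuming 56/3 per class) and about one percentage point of power. It does not give the other four Wave 2 IG-run classes (2 male, 2 female) a same-wave CG-run comparator; that limitation remains.

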### Intervention

#### Development process of the intervention

In Phase 1, which began in January 2016, we started to develop the run/game play intervention for GEKOS and made first drafts of the intervention contents (Fig. 2, Phase 1a). We conducted a literature research regarding health and physical fitness in PE [13] and reviewed the PE-curricula of all German federal states regarding the PAHCO model. In conjunction with teachers and experts in education, we progressed to a first intervention draft for the run/game play intervention. Next, two focus groups discussed both intervention programs with an emphasis on the method, implementation, and comprehensibility of the lesson plans (Phase 1b). In Phase 1c (January 2017), five teachers tested the feasibility of the first four lessons in Pilot Study 1 (2 female and 3 male teachers). At the end of Phase 1, an initial treatment manual was generated.

**Fig. 2 Fig2:**
[figure not shown]
A diagrammatic representation of the development of the finalized treatment manual and fidelity protocol (following Toomey et al. [30])

In Pilot Study 2 (Phase 2), eight teachers (2 females and 2 males per intervention) and their students (*n* = 140) tested the feasibility of the initial manual in practice. We also evaluated the teacher training, assessment strategies (physical fitness and written tests), and fidelity measures (self-report forms for teachers in a checklist style [30] and surveillance sheets).

In both pilot studies, we observed each lesson and assessed these lessons using a formative evaluation, which was later discussed with the teachers in a semi-structured interview. We also asked the students for their opinions using a written questionnaire.

#### Contents of the intervention

The final intervention programs include six PE lessons that are each 90 min in duration. The participating PE teachers of the intervention groups conduct these lessons consecutively within the intended timeframe of 6 weeks. All six PE lessons focus on health and physical fitness and contain the two main topics of the perception of physical load as well as the control of physical load and physical training. In all lessons, students are physically active and also reflect on-action and in-action (“reflective practice”, [23, 33]). Therefore, the lessons include both practical and theoretical elements dealing with the perception and control of physical load as well as the design of a training program to promote health as central aspects of control competence for physical training. The two intervention programs only differ in the type of PA that is carried out during these lessons; the run intervention involves running and jumping activities, while the game play intervention focuses on small-sided games (SSG) and soccer as well as handball drills.

During the development of the intervention programs (Phase 1, Fig. 2), we defined six learning outcomes for the intervention programs, which were used as a framework to define the intervention programs’ content. The intended outcomes for students are as follows:Perform and pace aerobic and muscle strengthening PA.Perceive as well as explain physiological responses to PA (e.g. increasing heart rate) during aerobic or muscle strengthening PA and use the physiological response to PA to regulate PA.Monitor and evaluate acute physiological responses to PA during PA using different techniques (e.g., rating of perceived exertion (RPE)).Name and explain the basic principles of exercise to plan an exercise program.Identify different types of PA and adjust components of the FITT formula (frequency, intensity, time, and type) to affect cardiovascular endurance and muscular endurance while considering a specific objective.Name the effects of PA on health and reflect upon the importance of PA for one’s own health.

To support students’ progress concerning the learning outcomes, we developed five learning tasks to guide the six PE lessons. These five tasks cover the two main topics of the perception of physical load as well as the control of physical load and physical training. Each of the five learning tasks includes six steps (Fig. 3), which align with the teaching and learning process for the promotion of competences as described by Leisen [34] that is comparable to the instructional method of problem-based learning [35]. For each step of the learning tasks (except Step 1), we included subtasks for the students to solve consecutively. After presenting the issue (Step 1: e.g., physiological responses during PA), the teachers invite their students to formulate assumptions on the topic (Step 2: e.g., assumptions about changes in the body during PA) without receiving immediate feedback. Subsequently, the students receive information on the topic while solving tasks that combine PA and cognitive elements by reflecting on-action (PA) or in-action (PA; Step 3). During Steps 4 and 5, the students discuss the given information and findings in relation to the lessons’ topic with their respective teacher (Step 4), thus, identifying right and wrong assumptions, and defining relevant outcomes (Step 5). Finally, the teachers ask the students to apply the new skills and knowledge (Step 6; see Fig. 3 for a detailed description of the tasks). All subtasks incorporate aspects considered important for the acquisition of competences in education, such as cognitive activation, student-orientation, and support social-interaction [24].

**Fig. 3 Fig3:**
[figure not shown]
Main topics and learning tasks of the six PE lessons. ^a^ Learning outcomes and their numbers are illustrated in the text. *LO* learning outcome, *GD* group discussion, *HR* heart rate, *RHR* resting heart rate

### Control group

PE teachers in the control group teach six consecutive regular PE lessons focusing on running and jumping activities (CG-run) or on games (CG-game play). We did not give them any guidelines concerning the methods or specific content (except physical activities) of their PE lessons. After the follow-up tests, control group teachers will have the opportunity to attend the same two-hour training session that teachers in the intervention received beforehand. We also will make the manual and materials of one of the intervention programs available to these control group teachers after the study has concluded.

### Measures

In order to test, revise, and optimize all measures before the main study, we applied the scales and physical fitness tests in Pilot Study 2 (Fig. 2). Furthermore, we tested all measurements (except for the physical fitness test) to assess the intervention-related aspects of PAHCO as well as the health and physical fitness as a subject of discussion in PE scale in a sample of 800 students in 2015 prior to beginning the pilot studies. Figure 4 shows a list of measurements of the main study at each time point.

**Fig. 4 Fig4:**
[figure not shown]
Measurements at each time point: baseline, post-intervention, 8–12 week follow-up, and process measures during the 6-week sessions (following SPIRIT template [31]). ^a^ administered in intervention group only. ^b^ once in each class covering each time point at least once. *w* week; *t* time point; *c* class

#### Intervention-related aspects of PAHCO

To measure the effect of the intervention programs on control competence for physical training, health-related fitness knowledge, physical fitness, and health and physical fitness-related interest and attitudes, the following validated measures are applied.

